**A. Background and hypothesis**

HIV/AIDS is a major contributor to morbidity and mortality in Uganda (UNAIDS, 2005). Despite years of consistent decline in incidence rates (USAID, 2002), recent data suggest rising incidence (Shafer et al., 2006; Kamali et al., 2002). Further, among young people between the ages of 15 and 24 years who engaged in higher-risk sex in the previous year, 38% of men and 56% of women did not use a condom (UNAIDS, 2005). Perhaps most telling, surveys suggest that HIV knowledge is on the decline among young people in Uganda compared to their same-aged counterparts surveyed in 1990 (UNAIDS, 2005).

New and innovative methods are needed to affect behavior change and promote HIV risk reduction strategies among young people. The Internet is a promising mode of intervention delivery in resource-limited settings because the costs associated with scaling up are minimal: dissemination of online material is the same if one person or 100,000 people use the program ([name] & Eaton, 2005). Just as important, it provides access to imperative health information in a stigma-free, anonymous atmosphere.

Our recent data published in PLoS indicate that 45% of adolescents in Mbarara, Uganda (a small municipality four hours outside of Kampala) have used the Internet, 78% of whom went online in the previous week ([name] et al., 2006). Already, one-third (35%) have looked for information about HIV/AIDS on a computer or the Internet. These data suggest that Internet-delivered adolescent risk reduction interventions are both desired and feasible in Uganda.

We will achieve the following objectives through this work:

**Objective 1:** Design a 6-hour, Internet-based HIV prevention program for adolescents. Content will be culturally tailored to the HIV preventive information, motivation, and behavioral skills needs of Ugandan adolescents.

**Objective 2:** Test the intervention in a randomized controlled trial (n=500) among adolescents attending grades Secondary 1-4 (similar to US high school grades 8th – 11th) at day schools in Mbarara.

The intervention program design will be focused on promoting HIV preventive behaviors. Acknowledging that adolescence is a time of sexual debut for a large minority of youth (UNAIDS, 2005), we use a harm reduction approach, reflected by our main outcome, which is abstaining from unprotected sex during the 6-months post-intervention. We also recognize that abstinence from sex is the most effective method of HIV prevention, and therefore include as a secondary outcome measure, sexual abstinence during the 6-months post-intervention.

In addition to the training session about how to use the intervention program, the Internet-based intervention will be a 6-hour course.

Topics covered.Content will be written to address the important characteristics affecting HIV preventive behavior as identified in our theoretical model and confirmed in the qualitative study: HIV prevention information, motivation, and behavioral skills. Anticipated intervention topics are informed by the adolescent focus groups conducted in Musaka, Uganda by Muyinda et al (Muyinda et al., 2003). Content will acknowledge social-contextual factors that affect the sexual behavior of young Africans (Kinsman et al., 2001), specifically: 1) a high value placed on pre-marital sexual activity; 2) peer pressure plays a large role as do social norms; 3) financial and material transactions are often involved in sexual intercourse; 4) although condom usage has increased, there remains frequent unprotected sex; and 5) there continues to be a gap between knowledge and continued risk behavior. We also expect issues about gender inequality, poverty, stigma, violence, coercion, and family functioning to emerge from the qualitative study findings. Figure 1 shows how these locally-identified topics map to our theoretical model.

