**B. Study procedure and methodologies**

To develop the HIV prevention web site, we will use a mix of qualitative and quantitative methods.

Our first step in intervention design will be to conduct a qualitative study to examine the applicability of the IMB Model to HIV preventive behavior among youth in Uganda. Integrating lessons learned from the formative data, the program then will be developed with direct feedback from adults and youth in the community. The program will be tested in an ongoing fashion during the design phase to ensure proper execution of lessons learned during the formative testing. Finally, the intervention and protocol will be tested in a randomized control trial of 500 adolescents attending one of the five secondary schools in Mbarara.

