The logistics of the randomized controlled trial will be complicated and difficult. To ensure that we are properly trained for the task, and that the schools have appropriate expectations of what we need to be successful when we are in field, we are proposing to add a Methodology Pilot. We will recruit, randomize, and follow 96 students (24 in each school) through a randomized controlled trial of MoodGYM, a five-lesson Internet program aimed to change thoughts and behaviors to improve depressive symptomatology. Half will be randomly assigned to the internet program; half will be assigned to the comparison group. We will focus on solving logistical challenges relevant to the randomized controlled trial including challenges involved in transferring a large number of secondary students from school to the Study cafe multiple times per week, adhering to a well scripted schedule that takes into account our Study cafe capacity and school activities, and examining whether students are willing to complete a multi-week Internet program. Also, we will be conducting the baseline and follow up surveys online to confirm that data can be validly collected in this mode.

Participants in the comparison group will be asked to come to the study office two times. The first time, they will complete a survey on the computer. Three weeks later, they will return to the study office and complete a second survey. Participants in the MoodGYM group will be asked to come to the study office seven times over three weeks. The first time, they will complete a survey on the computer. They will complete one MoodGYM lesson for the next five visits, each. On the seventh visit, they will complete the second survey. All students will complete the same surveys. Questions will include things about their feelings including depression, their experience with computers and cell phones, and also things about their relationships with friends and boyfriends or girlfriends. Students assigned to the MoodGYM program also will answer questions about their experience with the Internet program.

7. Randomized controlled trial (n=400):

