Once the Internet-based program has been developed, we will test it in an intent-to-treat, missing=failure randomized controlled trial among 400 randomly identified adolescents in Mbarara. Subjects meeting inclusion criteria will be randomized to either the intervention (n=200) or the control (n=200) study group. Participants in the Intervention group will complete intervention modules aimed at increasing HIV preventive behavior. They will come to the study café once a week to complete a one-hour module each session. Participants in the control group will be a treatment-as-usual group; they will receive the sexual health education available at their schools. All children will participate in data collection surveys at three different time points: at baseline, the beginning of school Term II, and the beginning of school Term III.

To gather feedback about and understand the experiences with the CyberSenga program, we will conduct six focus groups with intervention participants after the final quantitative follow-up data collection period. Participants will be randomly identified from among the intervention participants. Groups will be stratified by biological sex, and grade (senior 2 versus senior 3 and 4).

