# Participants in the youth one-on-one interviews (n=48) will be randomly selected from Sentah College (A above) and Mbarara secondary school (C above). Specifically 6 youth in each of the 4 grades in both schools will be selected. Youth participants in the quantitative survey (n=1496), technology assessment (n=20), the Methodology pilot (n=96) and the randomized controlled trial (n=500) will be recruited randomly from each of the five study schools.

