Recruitment for the Youth Advisory Council (n=20) will based upon peer-nomination so that they represent the opinion leaders of the target population. We will conduct a brief paper-and-pencil survey in Year 2 to measure the information, motivation, and behavioral skills associated with HIV preventive behavior among all youth in the target schools. Included in this survey will be one question about the student in their grade that youth look up to the most. The one student mentioned the most frequently in each of the four secondary grades within each of the five partner schools will be invited to take part in the YAC. If they decline, we will invite the second most frequently nominated student and so forth. If two or more students are equally popular, we will randomly choose one of the students to recruit.

Recruitment for the Community Advisory Board (n=20) will be based upon referrals from participants in the adult one-on-one interviews and people who work with adolescents that have relationships with research staff.

1. Expected number of individuals to be enrolled (+age, sex, ethnicity)

Below is the expected number of participants for the research project.

| Table 2. Expected number of individuals to be enrolled | | | |
| --- | --- | --- | --- |
| Research activity | n | Estimated length of involvement | Estimated place in project timeline |
| Individual interviews with adults | 15 | 1 hour | Year 1 |
| Individual interviews with adolescents | 48 | 1 hour | Year 1 |
| Quantitative survey | 1,496 | 1 hour | Year 2 |
| Technology assessment | 10 | 1-2 hours | Year 3 |
| Youth Advisory Council | 20 | 6-12 hours | Year 2-3 |
| Community Advisory Board | 20 | 6 hours | Year 2-3 |
| Methodology Pilot (MoodGYM) | 96 | 2 hours for control, 7 for the intervention | Year 3 |
| Randomized controlled trial | 400 | 4 hours for control, 10 hours for intervention | Year 4 |

We expect 100% of youth participants to be African. Sixty percent are expected to be male, although this is more a reflection of the schools (i.e., 2 are all-male; see Table 2) than of the recruitment strategy per se. In mixed-sex schools, we anticipate 50% of recruited participants will be female. The expected age range is between 12-18 years of age, although given our inclusion criteria based upon secondary grades 2-4, 80% of participants are expected to be between the ages of 14-17.

4. Randomization

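### The protocol gives the randomised trial's target as 500 in three places and 400 in three others; 400 fits the design sections, and the 500 text needs correcting together with its school count and grade range

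*Protocol*

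**What the plan says.** Three places put the trial at 500:

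- Section A, Objective 2: "Test the intervention in a randomized controlled trial (n=500) among adolescents attending grades Secondary 1-4".
- Section B, opening overview: "a randomized control trial of 500 adolescents attending one of the five secondary schools in Mbarara".
- Section C, Recruitment procedures, the paragraph after Table 1: "the randomized controlled trial (n=500) will be recruited randomly from each of the five study schools".

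Three places put it at 400:

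- Section B.7, heading: "Randomized controlled trial (n=400".
- Section B.7, design text: "randomized controlled trial among 400 randomly identified adolescents in Mbarara", with participants "randomized to either the intervention (n=200) or the control (n=200) study group".
- Section C, Table 2 (expected enrolment): "Randomized controlled trial | 400".

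The next paragraph of the recruitment text limits the trial's scope. From the methodology pilot onward four of the five schools are used, School E is out of both the pilot and the trial, and Secondary 1 is left out of the trial. The inclusion criteria in section C likewise name Secondary 2 through 4.

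**The concern.** The planned number of participants is a protocol commitment that recruitment staff, ethics boards and later readers of the results all rely on. Here the stated objective and the recruitment instruction give one number, while the design section and the enrolment table give another.

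Two practical consequences follow. Staff working from the recruitment paragraph would aim for 100 more adolescents than the arm sizes provide for. A trial that closed at 400, as section B.7 describes, would appear to have missed its own Objective 2. The participants are mostly minors, enrolled on the consent of a parent or school principal, so the approved number should be unambiguous.

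**Working it through.** **Does the design section add up?** Section B.7 gives 200 intervention and 200 control: 200 + 200 = 400. This equals the total in that section's heading and text and in Table 2. An equal split of 500 would be 250 per arm, and no place in the protocol gives 250.

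**Size of the gap.** 500 − 400 = 100 participants, or 50 per arm at equal allocation. 100/500 = 20%, so 400 is 20% below 500. 100/400 = 25%, so 500 is 25% above 400.

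**Could both numbers be right, as counts of different things?** One might read 500 as students approached and 400 as students randomised. The text does not allow it. Objective 2 and the section B overview attach 500 to the trial itself. The loss between selection and eligibility is dealt with separately in section C, by over-sampling at the screening stage until the target number of eligible students is reached, and no number is given for that over-sampling. No dropout allowance is stated either.

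**What else is in the sentences that say 500?**

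| Place | Trial size | Scope stated there | Scope in section C |
|---|---|---|---|
| Section A, Objective 2 | 500 | Secondary 1–4 | Secondary 2–4 |
| Section B overview | 500 | five schools | four schools |
| Section C recruitment paragraph | 500 | five schools | four schools |

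Each statement of 500 sits beside a statement of scope that section C contradicts.

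**Other signs that the recruitment paragraph is out of date.** It gives the technology assessment as 20, whereas section B.3 and Table 2 give 10. It also has the methodology pilot drawing on all five schools, whereas section B.6 plans 96 students at 24 per school, and 96/24 = 4 schools.

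**A possible origin of the two totals.** 500/5 schools = 100 per school, and 400/4 schools = 100 per school. This fits 500 being left over from a five-school plan. It is an inference; the protocol states no per-school quota for the trial.

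**Can either total be derived from a power calculation?** No. The protocol gives no significance level, power, outcome rate, effect size or dropout for the randomised trial. The only power analysis it mentions is for the quantitative survey.

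**The case against.** The strongest defence is that a careful reader can tell which number is meant. The section that defines the trial gives a total and both arm sizes, the enrolment table agrees, and the restriction to four schools and Secondary 2–4 belongs with that design. On this view the statements of 500 are leftovers, and no analysis in the protocol uses them. This largely stands, and it limits how far the point can go.

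Three stronger readings are tempting but not supported:

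- *The plan commits to two different trials.* A reader might infer this from the even count of three against three. Only one design is worked out, and it has 400 participants. What is contradictory is the stated target and scope.
- *Every operational section says 400, so only the background needs correcting.* The recruitment paragraph is operational and says 500.
- *Going from 500 to 400 costs the trial a definite amount of power.* Any such figure would need a starting power, outcome rate and effect size that the protocol does not give. No stated power claim is invalidated here. The absence of a power basis is not itself a finding, since it may be in a statistical analysis plan that was not available.

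The defence does not remove the defect. The protocol nowhere says which total is final, and the wrong number stands in the objective and in the recruitment instruction, where it is most likely to be read and followed.

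**Conclusion.** The point holds as an internal inconsistency in the planned sample size: 500 in three places against 400 in three others, a difference of 100 participants or 20% of the larger figure. The two totals themselves need no assumption. That 400 is the intended one is a well-supported inference: it rests on the arm sizes, Table 2 and the narrower school and grade scope, but the protocol does not confirm it. The school count and grade range are part of the same problem because they conflict with section C in the very sentences that state 500. No power loss is claimed. The correction is cheap, but it is more than clerical, because the trial's target enrolment is a figure that others rely on.

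**What to change.** 1. The sponsor confirms the target as 400, 200 per arm.
2. Replace 500 with 400 in Objective 2 (section A), the section B overview, and the recruitment paragraph after Table 1 (section C).
3. In the same edit, reconcile the scope with section C: the grade range in Objective 2 (Secondary 2–4), and the school count for the trial in the section B overview and the recruitment paragraph (four schools, without School E). Changing the number alone would leave these conflicts in place.
4. If a power or detectable-difference figure set at 500 exists in another document, restate it at 200 per arm.

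If the sponsor's answer is not 400, the heading and arm sizes in section B.7 and the row in Table 2 are what must change instead.

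The cost is protocol wording in three places. No additional enrolment is proposed, and neither the design nor the analysis changes.

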**HIV prevention motivation**

Attitudes

Peer pressure

Norms

Family planning

Value placed on pre-marital sex

Intentions

**Figure 1: Theoretical model and associated content area**

***HIV prevention behavior:***

*Use of condoms during sex*

**HIV prevention information**

HIV/AIDS education

STD education

Role of substance use in HIV (e.g., decreased inhibition)

**HIV prevention behavioral skills**

HIV testing and treatment seeking for STDs

Talking about sex

The role the women plays in partner communication (clear communication)

The role the man plays in unwanted sex (coercive sex)

Condom use and locally applicable information (i.e., where to obtain condoms in Mbarara)

Techniques for avoiding unwanted/risky sex

Delaying first sex

Partner reduction

**Interactive vignettes**

***Possible cultural factors:***

*Gender inequality*

*Poverty*

*Stigma*

*Violence*

*Coercion*

*Local access to condoms*

Based upon sex-specific norms and cultural beliefs, some modules will be tailored by sex (e.g., family planning, traditional sex practices). Culturally sensitive information and vignettes will be the backbone of the intervention, with the qualitative study findings driving the framework for the final content.

Content and interactive features. Given the unique cultural aspects of HIV education and behavior in Uganda, it is important that the intervention be developed within the community as opposed to modified from a Western program. We believe that the culturally appropriate, community-based intervention conducted by Muyinda et al (Muyinda et al., 2003) may provide a helpful framework from which to begin. Their use of surrogate sengas as narrators of intervention information and education was reportedly accepted not only by adolescent women but also adolescent men. Results of the study suggest increased HIV preventive behavior for both sexes in the intervention community versus control community.

Personal “guides” have been successfully used in the YouthNet project. Because the modern sengas were so resonant with young people in the earlier research (Muyinda et al., 2003; Muyinda et al., 2004), we propose to use this framework by including virtual sengas as ‘guides’ through the intervention. As a personalized character within the online course, the senga will introduce each topical area and then narrate the program as the topic is further elucidated. Communication strategies and behavioral skills will be reinforced through vignettes played out by role models matched to the user by age and sex. Important aspects of the vignette will be punctuated both by text and by the senga’s narration as was done successfully in YouthNet. We will confirm the saliency of the virtual senga as well as explore other possible narrators that young people find relevant and compelling among both adolescent women and men during the focus groups and Youth Advisory Council module testing.

Program exercises will be informed by Fisher et al’s (Fisher et al., 2002) Information-Motivation-Behavior skills HIV risk reduction intervention developed for youth, which has demonstrated HIV behavior change across many different groups of young people (Fisher et al., 1994; Fisher et al., 2002; Bryan et al., 2000; Linn.J.G. et al., 2001; Kalichman, 2005). Module 1 will focus on teaching correct **information** about HIV transmission and prevention, paying special attention to correcting common misperceptions identified during the qualitative study. Module 2 will focus on promoting **motivation** to change behavior by targeting norms and attitudes among adolescents in Mbarara illuminated in the qualitative study that lead to risky behavior. For example, depending on the qualitative study findings, we may examine peer pressure to have sex, financial and material transactions that can accompany sex, and the value placed on pre-martial sex among adolescents in Mbarara. Module 3 will reinforce motivation for behavior change through videos and cartoons. Module 4 will focus on the teaching of **behavioral skills** necessary for condom use and abstinence. Module 5 will focus on communication skills and teaching youth how to negotiate safer sex scenarios. Module 6 will interactively review the information, motivation and behavioral skills learned in the previous 5 modules.

**B. Study procedure and methodologies**

To develop the HIV prevention web site, we will use a mix of qualitative and quantitative methods.

Our first step in intervention design will be to conduct a qualitative study to examine the applicability of the IMB Model to HIV preventive behavior among youth in Uganda. Integrating lessons learned from the formative data, the program then will be developed with direct feedback from adults and youth in the community. The program will be tested in an ongoing fashion during the design phase to ensure proper execution of lessons learned during the formative testing. Finally, the intervention and protocol will be tested in a randomized control trial of 500 adolescents attending one of the five secondary schools in Mbarara.

### 1. One-on-one interviews (n=15 adults, 48 youth):

### We will use a qualitative approach to examine the applicability of the IMB model to the study of HIV-preventive behavior among youth in Uganda.

### First, individual semi-structured interviews will be conducted with 15 key adult informants who are “experts” on adolescent behavior and local culture. We will ask for their thoughts on adolescents’ ideas about HIV transmission, the motivations youth may have for engaging in unprotected and protected sex, and the behavioral skills young people have to engage in HIV risk reduction behaviors. Information gathered will be used to identify and refine concepts to be explored later in interviews with adolescents (see Appendix A).

